## PHASE 2: IMPACT AND ACCEPTABILITY OF SYSTEMATIC FAMILY HISTORY COLLECTION: AN EXPLORATORY MATCHED-PAIR CLUSTER RANDOMISED STUDY

This phase of the project seeks to evaluate the impact of systematically collecting relevant premature CHD family histories. The data collected will be both quantitative, in terms of the number of extra participants identified and self-reported behavioural and psychological measures, and qualitative, in terms of the experience of participants and professionals involved. The results of this phase will inform outcomes 2 and 5 and achieve outcomes 3 and 4. Qualitative interviews will explore the processes that lead to the quantitative outcomes and evaluate social, cultural, service-related factors and ethical concerns that affect the acceptability and effectiveness of the intervention. Qualitative research has successfully been incorporated into randomised studies testing complex behavioural interventions in order to explore the acceptability of the intervention[25] and to examine the psychosocial processes that lead to the quantitative outcomes[26,27]. Focus groups will facilitate a participatory dialogue between clinicians on the acceptability and feasibility of the intervention[28].

### Methods

#### Study Design

A pragmatic exploratory matched-pair cluster randomised study with a nested qualitative semi-structured interview and focus group project. Practices from the Trent and Peninsula research networks will be invited to participate in the study. Researchers at both sites will visit interested practices to explain the research project. Twelve pairs of eligible practices, who agree to participate, will be recruited (6 pairs from South West England and 6 pairs in the East Midlands). The practices will be paired according to level of deprivation (as per Indices of Multiple Deprivation (IMD) quintiles), and ethnicity (as per more or less than 10% non-White population) in their specific electoral wards. One of each pair will be randomly assigned to the standard CVD risk assessment procedure, whilst the other practice within the pair, in addition to providing a standard CVD risk assessment, will also take account of premature CHD familial risk using the family history questionnaire (FHQ). Randomisation will be stratified by study centre. The matched-paired allocation scheme is demonstrated in figure 1. The randomisation list will be prepared centrally by an independent data manager at the University of Nottingham Clinical Trials Support Unit (CTSU). The random allocation sequence will be generated by a computer programme and the treatment allocation for each practice will be obtained by a password-protected internet link. The practices, research staff and participants will not be blinded to group assignment but the study statistician will be. For the statistical analysis treatment arms will be distinguished by a code assigned by the independent data manager at the CTSU. The meaning of these codes will not be revealed to any members of the research team until data analysis is complete. Figure 1 indicates the matched-pair allocation scheme used in this study.

**Figure 1 F1:**
[figure not shown]
**Matched-Pair Allocation Scheme**. T = Trent, S = Southwest, Tc = control site in Trent, Sc = control site in Southwest, Ti = intervention site in Trent, Si = intervention site in Southwest.

The nested qualitative study will recruit participants in both the intervention and control arms, who have been assessed to be at high risk of heart disease (20% or above risk in the next ten years). We expect the impact of the assessment to be strongest in this group, and qualitative interviews will yield insights into how participants cope with being defined as at high risk, what behavioural and psychological impact this risk information has and how the response is mediated by individual and social contexts. Conducting the interviews with participants in both intervention and control arms allows for exploring whether family history assessment renders the participants' experience different and how.

After the recruitment for the study has been completed, six practices in the intervention arm (3 in the East Midlands and 3 in the South West) will be invited for a focus group. The focus groups will seek to solicit clinicians' views on the acceptability, feasibility and usefulness of the family history assessment; it will also invite the clinicians to discuss their usual practice in terms of taking family history of heart disease.

#### Study interventions

##### FHQ group

Detailed CHD family history information will be collected by participants completing a CHD focused validated Family History Questionnaire (FHQ) (already developed and evaluated by the research team)[22]. The effect of incorporating this information into the standard CVD risk assessment procedure and the subsequent advice given to participants on CVD risk and lifestyle will be assessed.

##### Control group

Participants will have their CVD risk assessment score calculated using the standard CVD risk assessment procedure.

##### Details of planned interventions

Participating clinicians in both groups will be given standardised training, including interpreting CVD risk, standard evidence/consensus based messages for lifestyle change. Clinicians in the FHx will in addition, be given information on interpreting and communication about the risk associated with family history of premature CHD, based on our pilot study[23]. To enhance the standardisation of the training, initial training sessions in both arms on both study sites will be video recorded, compared and fed back to the trainers.

#### Eligibility criteria

The eligibility criteria will ensure the inclusion of multi-ethnic and socio-economically deprived areas.

#### Practice level eligibility criteria

##### Inclusion Criteria

▪ To be within either Trent Primary Care Trusts in Nottinghamshire and Lincolnshire or the area served by the Peninsula Primary Care Research Network in Devon and Cornwall.

##### Exclusion Criteria

▪ General Practices outside of these PCTs/networks will be excluded.

#### Participant level eligibility criteria

##### Inclusion criteria

▪ Patients between 30 and 65 years of age.

##### Exclusion criteria

▪ Patients noted to have a previous history of atherosclerotic disease (this includes CHD, CVA & Peripheral Vascular Disease)

▪ Previous history of Diabetes Mellitus

▪ Patients already on statin therapy or other lipid lowering medications

▪ Patients considered by the General Practitioners to be inappropriate to recruit due to psychosocial and other reasons.

#### Recruitment

Patients, who are offered CVD risk assessment and referred for a cholesterol test as part of their normal care (either at their doctor's initiative or at their own request), will be invited to participate. These patients will be recruited opportunistically, as they present to the GP and practice nurse for a CVD risk assessment. They will be given a study pack, which includes consent forms, participant information sheet, collection of information on CHD risk factors (age, gender, ethnicity) and baseline outcome measures. Participants in the FHQ group will be given, in addition, the Family History Questionnaire. The completed baseline questionnaires and consent forms will be sent to the research team or handed to the practice receptionist, who will forward them to the research team.

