Primary prevention of CHD through lifestyle advice has sometimes yielded modest results[11] although, for example, behavioural interventions targeted at "at risk" patients have produced encouraging findings[12]. There is evidence that interventions that have targeted the family as a whole, rather than individuals, are more effective[13], and it has been reported that young individuals who were aware of their family history of CHD were less likely to smoke[14]. This evidence suggests that a family history approach, targeted at "at risk" individuals and those requesting CHD assessment, could motivate lifestyle change. However, it has been suggested that assessment of inherited risk may produce fatalism or anxiety[15], although these findings have not been corroborated in other studies[16]. Furthermore, people from different backgrounds have different understanding of the causes of heart disease; research has also discovered varied "lay models" of the risk associated with a family history of heart disease [17-19]. In light of these findings, it has been emphasized that to be effective, CHD prevention needs in-depth sensitivity to the ethnically and socioeconomically diverse patients' personal and cultural models of disease and family history [17,20]. Still, patients' interpretations of, and reactions to, incorporating family history into CHD risk assessment have not been studied. We have previously explored the psychological impact of a general family history questionnaire (FHQ)[21] and the validation of this instrument [22]. We have completed a qualitative pilot study on the feasibility of incorporating family history into CHD assessment from a risk communication point of view [23]. However, in order to inform policy the assessment of the clinical utility of using family history is now needed as a priority, alongside work such as that by the CDC Family HealthWare project, and prior to the development *de novo *of further tools[6]. This should include examination of the behavioural and psychological effects of CHD interventions using family history assessment. Moreover a better understanding of the implications of being identified as at higher risk of heart disease (due to a family history of premature CHD), for individuals from different social and ethnic backgrounds is also needed.

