The project will assess the clinical value and utility of incorporating systematised family history information into Coronary Heart Disease (CHD) risk assessment in primary care, from the perspective of the users of this service, the health care practitioners providing this service, and the National Health Service. Current CHD risk assessment guidelines express CHD risk within cardiovascular disease (CVD) risk assessment, with patients divided into three broad risk categories based on the risk of CVD in the next 10 years: Average risk (less than 10% CVD risk), Moderate risk (10% to 19% CVD risk), and High risk (20% or greater 10 year CVD risk)[1].

This three-phase project will assess the clinical value of incorporating systematic family history information into the standard CVD risk assessment in General Practice, by:

1 Estimating the extra proportion of participants at high risk of CHD, who would benefit from intensive lifestyle advice and medications, when incorporating systematically collected family history into the risk assessment, in comparison with current practice.

2 Comparing changes in self-reported behaviour, anxiety and social/psychological experience, between individuals who have been allocated to either CVD risk assessment using (i) standard risk assessment complemented by systematic collection of family history or (ii) standard risk assessment alone (usual care).

Further, there will be an assessment of general practitioners' and practice nurses' views on the feasibility and acceptability of incorporating family history into routine CVD risk assessment.

To achieve these goals, the project will include three distinct phases: (1) ascertain baseline information on current recording of family information, (2) assess, through an exploratory randomised study (including quantitative measures, qualitative semi-structured interviews and focus groups), the impact of systematic family history recording on participants' and primary care professionals' experience, and (3) develop an economic model of the costs and benefits of incorporating family history into CVD risk assessment. Phase 1 will provide information on the impact of CHD family history currently available in GP records on CVD risk assessment, with which the systematic collection of CHD family history (in Phase 2) will be compared, to assess the additional value of the latter intervention. Phase 3 will assess the benefits of systematic collection through health economic analyses.

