#### Outcome measures

The primary outcome measure is the proportion of participants falling in the high risk of CVD category

The secondary outcome measures are:

i) Self-reported lifestyle changes; including changes in smoking habits, levels of exercise and fat intake[29,30]

ii): Anxiety, using the 6 item Spielberger State-Trait Anxiety Inventory (STAI)[31] and fatalism and causal attributions of heart disease using the Illness Perception Questionnaire[32,33]

iii): Perception of health-related quality of life (SF-6D, derived from SF-36, and global question 2)[34,35].

The first two groups of these measures have been used in the assessment of CHD prevention in UK primary care. Perception of health and 6 item STAI measures have been used in other studies on family history and genetic screening in primary care[21,36,37].

Qualitative interviews will be used to analyse the contextual processes that mediate lifestyle change and risk perceptions of participants identified as at high risk in both the control and the FHQ group of the study. Participants' changes in views and their perceptions of heart disease, family history, their personal risk, lifestyle, medications, ethical concerns and their social, cultural and familial context will be collected.

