#### Ethical considerations

We do not foresee major ethical issues arising from our study. Filling the FHQ may transiently raise patients' anxiety[21], but we are recruiting patients who have either requested CVD risk assessment themselves or been offered it by their doctor, so we are not increasing anxiety in a previously unaware population. We will follow normal ethical procedures to ensure informed consent, confidentiality and data protection.

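### In the FHQ arm the Family History Questionnaire is handed out with the baseline measures and no order of completion is set, so baseline anxiety may already be raised in that arm and a later effect on anxiety understated

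*Protocol article*

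**What the plan says.** All references are to the protocol article.

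- **Recruitment.** Patients in both arms receive a study pack with consent forms, information sheet, "collection of information on CHD risk factors (age, gender, ethnicity) and baseline outcome measures". The next sentence reads: "Participants in the FHQ group will be given, in addition, the Family History Questionnaire". Forms come back later: "The completed baseline questionnaires and consent forms will be sent to the research team or handed to the practice receptionist". Nothing says which form is filled in first.
- **Study interventions, FHQ group.** Completing the FHQ is how the intervention collects family history. It is part of the treatment under test.
- **Ethical considerations.** "Filling the FHQ may transiently raise" patients' anxiety. No size is given.
- **Outcome measures.** Anxiety (6-item STAI) is a secondary outcome. The primary outcome is the proportion classified at high CVD risk.
- **Background, second aim.** "Comparing changes in self-reported behaviour, anxiety and social/psychological experience, between individuals" in the two arms.
- **Data analysis.** The main time point is 6 months. A participant counts as complete only with the outcome at baseline and at 6 months. Adjustment is for variables associated with the outcome, and the baseline score is not named among them. One sensitivity analysis sets a missing 6-month value equal to baseline.

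**The concern.** A baseline should be measured before the arms are treated differently. Here a component of the intervention, which the protocol expects may raise anxiety for a time, reaches one arm together with the form that records baseline anxiety. A participant who fills in the FHQ first gives a post-exposure baseline, and this cannot happen in the control arm.

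Any analysis that subtracts or adjusts for that baseline then credits the FHQ arm with a fall in anxiety, or a smaller rise, that is partly an artefact. The error runs towards reassurance on an outcome included to detect psychological harm. An analysis plan can choose a contrast that avoids the baseline, but it cannot recover a clean baseline once the forms have been collected this way.

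**Working it through.** The plan states no figure on this point, so there is none to reproduce. The check is algebra on an outcome scaled to SD 1, with higher scores meaning more anxiety.

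**Inputs.** None of these sizes is in the documents; all are assumptions.
- d = mean upward shift of baseline anxiety in the FHQ arm: 0.2 to 0.3 SD.
- b = slope of the 6-month score on the baseline score within arm: 0.4 to 0.6.
- h = true later effect on anxiety at 6 months: 0 or 0.2 SD.

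**Formulas**, for a shift that has gone by 6 months (the protocol calls it transient):
- Plain 6-month contrast = h
- Change-score contrast = h - d
- Baseline-adjusted contrast = h - b x d

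**Results (SD):**

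| d | b | Change, h = 0 | Adjusted, h = 0 | Change, h = 0.2 | Adjusted, h = 0.2 |
|---|---|---|---|---|---|
| 0.2 | 0.4 | -0.20 | -0.08 | 0.00 | 0.12 |
| 0.2 | 0.6 | -0.20 | -0.12 | 0.00 | 0.08 |
| 0.3 | 0.4 | -0.30 | -0.12 | -0.10 | 0.08 |
| 0.3 | 0.6 | -0.30 | -0.18 | -0.10 | 0.02 |

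The plain 6-month contrast is 0 or 0.20 in every row. A simulation with 200,000 participants per scenario agreed with these values to within 0.012 SD.

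**If the FHQ's own effect persists to 6 months** with no further harm, the true contrast is d. The change score gives d - d = 0. Baseline adjustment gives (1 - b) x d, which keeps 60% of the effect at b = 0.4 and 40% at b = 0.6.

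**What d means.** It is an average over the arm. If only half of the FHQ arm fills in the FHQ first, d of 0.2 to 0.3 SD needs an effect of 0.2/0.5 = 0.4 to 0.3/0.5 = 0.6 SD in those who do. Smaller shifts scale down in proportion: d = 0.1 gives a bias of -0.10 for the change score and -0.04 to -0.06 with adjustment.

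**Baseline carried forward.** The Attrition rate section expects 60% to complete the 6-month questionnaire, so about 40% would take their baseline value. With equal loss in both arms and no later harm, a contrast of the resulting 6-month scores moves by 0.4 x d, or +0.08 to +0.12 SD: the opposite direction. If change scores are used instead, the carried-forward participants contribute a change of zero in both arms.

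**The case against.** The strongest reply is that the article is condensed. It says the FHQ is given in addition, but not how it is packaged or in what order the forms are completed, and the full protocol may settle both. The baseline score is not named as a covariate, the outcome is secondary, and the study is labelled exploratory. All of this stands and limits the point to a risk. It does not remove it: as written, the two forms arrive together in one arm only, and the stated aim and data requirement both rest on the baseline.

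Several stronger readings are tempting but not supported:

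- **That the FHQ-arm baseline is post-exposure.** No order is stated, and some or many participants may complete the baseline measures first.
- **That later harm is adjusted away.** With covariate adjustment the loss is b x d, which is partial in these scenarios. It is complete only with a change score, and then only if the shift is at least as large as the later effect or the FHQ effect merely persists.
- **That causal beliefs, fatalism or SF-6D (and so the QALY estimate) are affected.** The protocol's statement about filling in the FHQ concerns anxiety only. In the Background, "it has been suggested that assessment of inherited risk may produce fatalism or anxiety", but this is about assessing inherited risk, and the same sentence says other studies did not corroborate it.
- **That evidence of comparability is lost.** Matching of practices on deprivation and ethnicity, the demographic items and the standard CVD risk score all remain.
- **That the form causes different consent by arm.** Participants are unblinded and recruited after their practice is allocated, so willingness to join could differ whatever the packaging. That is a separate matter.

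**Conclusion.** The point holds as a modest, avoidable risk to one secondary outcome. Some FHQ-arm participants may report baseline anxiety after completing a form that the protocol says may raise it. The anxiety effect would then be understated by d with a change score or by b x d with baseline adjustment, and an unadjusted 6-month contrast would not be biased by this route. Carrying the baseline forward would err the other way when the resulting 6-month scores are compared, so that sensitivity analysis could disagree with the main analysis for an artificial reason.

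The direction follows from the text if some participants fill in the FHQ first and their anxiety rises. The size rests entirely on assumed values of d and b. The primary outcome is not a self-report scale and is untouched.

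**What to change.** 1. Keep the FHQ in the recruitment pack, but in a separate sealed envelope with an instruction to complete consent and the baseline measures before opening it. Otherwise give both arms the same baseline pack. If the order is already controlled, one sentence saying so is enough.
2. Report the 6-month anxiety contrast without baseline adjustment as a sensitivity analysis.

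Posting the FHQ only after the baseline forms return would separate the two more firmly, but it is not recommended as the main remedy. The risk letter goes out two weeks after the original consultation, and the FHQ must be back and scored for the primary outcome.

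**Cost.** An envelope and an instruction sheet. Some participants will ignore the order. The unadjusted analysis is less precise: ignoring clustering, its standard error is larger by a factor of 1/sqrt(1 - b^2) when baseline and 6-month SDs are equal. That is 1/sqrt(0.84) = 1.09 at b = 0.4 and 1/sqrt(0.64) = 1.25 at b = 0.6, which is acceptable for a sensitivity analysis.

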#### Data collection procedures

After initial recruitment, all participants will have their medical records reviewed to reconfirm their eligibility. On arrival of the cholesterol blood results, CVD risk scores will be calculated by the research team, as per JBS2 guidelines[1]. In the FHQ group, familial CHD risk will also be calculated and incorporated into the overall score. Two weeks after the original consultation both clinicians and participants will be sent a letter informing them about the participant's risk status. Participants identified at average or moderate CVD risk in both groups will be sent a letter confirming status together with a leaflet on lifestyle advice. In addition to a leaflet, those at higher risk in both groups will be informed that they are at higher than average CVD risk and invited for a consultation in the practice within the next 2 weeks.

In the consultation with doctor or nurse, participants will have their CVD risk explained and given lifestyle advice and, when clinically indicated, statins will be offered, as per usual practice. Participants in the FHQ group will also have the impact of premature CHD family history on the CVD risk score explained.

At two weeks and six months after the second consultation (for high risk participants) or letter being sent (for average or moderate risk participants) all participants will be posted a set of questionnaires. Participants, who have been identified at high risk, will be invited for a qualitative interview by phone, following a purposeful, maximum variation sampling strategy in terms of being in intervention or control arm, gender, age, occupational class, ethnicity, region and having or not having a family history of premature CHD. Recruitment will continue until thematic saturation is reached. Participants in the qualitative study will be interviewed by an experienced researcher in their homes (or if the participants so desire by phone) at 2 weeks and 6 months after the consultation in the practice.

Six practices in the intervention arm will be invited to participate in a focus group to capture the practitioners' views on using family history assessment and incorporate this into their clinical decision making.

After nine months the recruited participants' computer GP records will be reviewed for prescribing of: lipid lowering, anti-obesity, and anti-thrombolytic drugs, as well as nicotine replacement therapy.

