## PHASE 1: BASELINE CVD RISK ASSESSMENT WITH/WITHOUT CURRENTLY AVAILABLE INFORMATION ON CHD FAMILY HISTORY IN GP RECORDS

During this phase, the inclusion of currently collected information about family history of premature CHD in General Practice records on CVD risk assessment will be assessed. The results of this phase will inform outcome 1. This entails a cross-sectional survey to examine the current collection and retrieval of family history data in GP manual records. The impact on absolute CVD risk scores of premature CHD family history will be informed by consensus. Using GP records, standard CVD risk assessment will be compared with risk assessment resulting from the inclusion of previously collected CHD family history in GP records.

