#### Data management

The FHQs and outcome questionnaires will be anonymised, given a unique identifier and then entered onto a database. An Access database will be specifically designed to monitor returns from each participating practice using consecutive numbering. The identifiable data will be stored securely at one site and this information will not be linked to actual socio-economic data, CVD risk assessment variables, family history and outcome measures; the unique identifier will be used for this purpose.

The Access administration database will include fields for age, gender, consent to participate, post code and sub-sample agreeing to be interviewed. Each week a printout will be generated providing details of participants who need to be contacted and sent the postal survey. The returning data will then be entered onto the main database using the participant's unique identification number.

Quality control in data entry: a 1 in 2 sample of the first 200 lifestyle outcome questionnaires at baseline and 2 weeks will be rechecked to identify errors in entry. Error rates greater than 0.5% will lead to double checking of all data entry. All CVD risk assessment scores will be checked by a second member of the team.

Interview and focus group audiotapes will be transcribed verbatim (no names or other identifying details will be included), and stored separately and securely away from transcripts.

The data will be stored for ten years on completion, in a locked filing cabinet within the researcher's employing organisational premises, in accordance with the Sponsor's requirements. Electronic data will be stored in an anonymised format and will also be encrypted.

All members of the research team will work within the principles of the Data Protection Act (1998) and Caldicott and Research Governance.

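### Unblinded research staff calculate the score that decides the primary outcome, and the planned second check is not described as masked; a fixed input rule and a locked base score would cheaply limit the risk

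*Protocol article*

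**What the plan says.** All references are to Phase 2 of the protocol article unless stated.

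- **Outcome.** Outcome measures: "The primary outcome measure is the proportion of participants falling in the high risk of CVD category". The Background defines that category as "High risk (20% or greater 10 year CVD risk".
- **Who scores.** Data collection procedures: "On arrival of the cholesterol blood results, CVD risk scores will be calculated by the research team, as per JBS2 guidelines[1". It continues: "In the FHQ group, familial CHD risk will also be calculated and incorporated into the overall score".
- **Blinding.** Study Design: "The practices, research staff and participants will not be blinded to group assignment but the study statistician will be". The same section has the arms coded for the analysis.
- **Checking.** Data management: "All CVD risk assessment scores will be checked by a second member of the team". Nothing is said about what the checker may see.
- **Family history weight.** Phase 1: "The impact on absolute CVD risk scores of premature CHD family history will be informed by consensus". The starting point is the guideline factor of about 1.5 quoted in the Background.
- **Analysis.** Data analysis compares the proportion at high risk between arms with a weighted paired t-test. It also promises to present the increase in that proportion that comes from adding family history.

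**The concern.** The primary outcome is a threshold crossing, and the difference expected between arms is small. The people who calculate the score know the arm. Because randomisation is by practice, the practice name alone reveals it. In the FHQ arm the questionnaire goes out in the recruitment pack, while scoring waits for the cholesterol result. The scorer can therefore hold the family history before the score without it is settled.

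The Background lists blood pressure and smoking status among the inputs to standard scores. If more than one recorded value is available, knowing the arm or the family history could influence which one is used for someone near 20%. A few such choices in one direction would move the arm difference. The statistician's blinding cannot undo this, because it starts after the scores exist. A second checker who sees the same information may catch arithmetic slips and still share the first scorer's expectation.

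**Working it through.** **1. The plan's own figures.** Sample size assumes 0% against 3%, 80% power, two-sided 0.05 and 265 per group. A two-sided Fisher exact test with no events in control needs at least 6 events in the other arm. With X ~ Bin(265, 0.03), P(X ≥ 6) = 80.8%, so 265 is reproduced. The design effect is 1 + (40 − 1) × 0.01 = 1.39, and 265 × 1.39 = 368.35, rounded up to 369, as stated. Masking the scoring does not change these numbers.

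**2. The planned effect in people.** Attrition rate expects 400 per arm with a completed risk assessment. 0.03 × 400 = 12 (and 0.03 × 369 = 11.07). This count does not depend on the baseline proportion.

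**3. Size of a possible shift.** The article gives no figure for reclassification caused by scoring, so k, the net number moved across 20% in one direction in one arm of 400, is an assumption. Bias = k/400; share of the planned effect = (k/400)/0.03.

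| k | Bias (points) | Share of planned effect |
|---|---|---|
| 0 | 0 | 0% |
| 1 | 0.25 | 8% |
| 2 | 0.50 | 17% |
| 4 | 1.00 | 33% |
| 6 | 1.50 | 50% |

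**4. Effect on type I error, as an illustration.** Assume no true difference, a control proportion of 5% (Phase 1, Sample Size, says at least 5%), 400 per arm and design effect 1.39, so the effective n is 400/1.39 = 287.8. Let b be the bias, p_t = 0.05 + b, and p̄ the mean of 0.05 and p_t. Then SE0 = √(2p̄(1 − p̄)/287.8), SE1 = √((0.05 × 0.95 + p_t(1 − p_t))/287.8), and the rejection rate is Φ((b − 1.96·SE0)/SE1) + Φ((−b − 1.96·SE0)/SE1). For b = 0, 0.5, 1.0 and 1.5 points this gives 5.0%, 5.8%, 8.2% and 12.1%. It is a two-proportion approximation, not the planned weighted paired t-test.

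**5. Which result is exposed.**
- *Between-arm proportion at high risk.* Anyone near 20% in either arm can be moved, with or without a family history, and nothing cancels.
- *Within-person increase in the FHQ arm.* The same base score enters both terms. For a participant with no qualifying family history the two scores are equal, so the increase is zero whatever the base error. A remainder survives near the thresholds. With the factor 1.5 as an illustration, someone truly at 20.5% but scored 19.5% becomes 19.5 × 1.5 = 29.25% and counts as newly identified, though already at high risk. The error can also run the other way: someone truly at 19.5% but scored 20.5% is not counted as new.

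**The case against.** The strongest reply is that the mechanism is assumed. Scoring follows a published guideline, every score is checked by a second person, and no sentence says that staff choose among readings or class smoking at their discretion. Abstraction rules are also detail that a condensed article commonly leaves to the full protocol. This stands. The article neither shows nor excludes discretion, and k = 0 is compatible with it. The point therefore rests on what the article does state, which is that the scorers are unblinded.

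Second, that the checker is unblinded is an inference. Data management does not say so. It follows from Study Design, which describes research staff as unblinded without exception. Anonymising the forms ("The FHQs and outcome questionnaires will be anonymised, given a unique identifier and then entered onto a database") removes identity, not arm, since only one arm has an FHQ.

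Third, part of the remedy is implied already. Presenting the increase from family history requires a score without it, and the weight is to be informed by consensus. That is fair. What is missing is the explicit order of steps and the masking.

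Fourth, a masked check that only recalculates from the inputs already abstracted cannot detect a biased choice of reading. This also stands, so the fix has to reach the inputs.

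A reader might infer that family history scoring itself should be masked to arm. It cannot be: it is the intervention and exists in one arm only. What can be protected is the base score common to both arms.

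**Conclusion.** The point holds as a cheap improvement. The score that decides the primary outcome is calculated by staff stated to be unblinded, and the second check has no stated masking. Bias is possible and is not shown. Its size is conditional: 0 to 6 people net in one arm of 400 correspond to 0% to 50% of the planned 3-point effect, and that range is an assumption.

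Two stronger readings are tempting and unsupported. One is that scoring will create a given part of the effect, for instance a third. That is arithmetic on an assumed four people, who must all move in one direction and survive a check of every score. The other is that any base-score error passes into the reported increase from family history. Within a person it largely, though not fully, cancels, and what remains can go either way. The between-arm comparison under Data analysis is where the exposure mainly lies.

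**What to change.** Under Data collection procedures, state three things:

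1. The JBS2 inputs are taken by one written rule, identical in both arms, for example on which recorded blood pressure and which source of smoking status are used.
2. The score without family history is calculated and locked, in both arms, before any FHQ is opened.
3. The consensus family history weight is then applied to the locked score as a fixed step.

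Under Data management, state that the existing second check covers whether the inputs followed the rule as well as the arithmetic, and that it uses a sheet without practice, arm or FHQ data. For this to work, the sheet must show the candidate entries and not only the one chosen. Whoever abstracts the records may still know the practice, and hence the arm. The fixed rule, verified by the masked check, is what limits that person's discretion.

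The cost is a change in the order of steps, one masked sheet and a slightly stricter workflow before letters go out. The second checker is already planned, so no staff or patients are added and the sample size is unchanged.
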